
#### Duration of treatment and follow-up

2.7.3

The study intervention will continue for 28 days following ICU admission, unless the patient is discharged from the ICU, discharged from the hospital, or dies earlier. All randomized patients will be followed for 90 days after ICU admission, unless death occurs first. If a patient remains hospitalized on day 90, follow-up will be conducted and outcomes will be recorded based on the patient’s status on day 90.

#### Reasons for withdrawal/discontinuation

2.7.4

If any serious adverse events related to the study occur during the trial, early withdrawal from the study will be permitted. In addition, if a patient or their legal representative requests withdrawal from the trial for any reason, early withdrawal will be allowed without affecting the patient’s future medical care from the investigators or study site. Efforts will be made to follow up all randomized patients to the extent permitted by their consent.

#### Exposure metrics, contamination and intervention fidelity

2.7.5

##### Exposure metrics

2.7.5.1

All participants receive a short-peptide formula from enrollment through study Day 3; this run-in period is not included in exposure analyses and is used solely for baseline standardization and tolerance assessment. Randomization occurs on Day 4 (D4). The exposure assessment window is D4–D7. We will record:

Duration of the exposure window (hours): elapsed time from randomization (D4) to 23:59 on D7 or to ICU transfer/discharge or death, whichever occurs first.Concordant feeding hours: cumulative hours during which the randomized formulation was actually administered.Adherence (%) = (concordant feeding hours ÷ exposure window hours) × 100. Interruptions (e.g., procedures, intolerance) will be time-stamped; calculations use actual accrued hours within the window.

##### Contamination

2.7.5.2

Within the exposure window, any administration (any dose, any single occasion) of a formulation not matching the randomized assignment is classified as contamination (patient-level binary; event-level counts recorded). To minimize contamination, the study coordinator will perform daily reconciliation of administered formula against the randomization list and notify the bedside team immediately upon discrepancy.

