#### Arm#2: Sequential Standard Polymeric Enteral Formula Group (SPF group)

2.6.2

Intervention. Transition from a PBF to an SPF after randomization.

Administration mode. Continuous pump infusion (gastric or post-pyloric).

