##### Intervention fidelity (adherence)

2.7.5.3

Fidelity is defined as complete execution of the feeding plan with the randomized formulation throughout the exposure window. Primary adherence is reported as the proportion of participants with 100% concordance; a secondary, continuous measure uses the adherence % defined above. If the attending physician changes the formulation for clinical reasons (e.g., fluid restriction, significant feeding intolerance), the reason must be documented, along with: start/stop timestamps of non-assigned formula, total time on non-assigned formula, and total exposure-window hours. Data sources: electronic medical records and clinical study report forms.

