##### CONSORT reporting

2.7.5.4

We will report (i) contamination rate, (ii) intervention fidelity, and (iii) duration of the exposure window (hours).

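### The exposure window opens at randomization with no changeover allowance, so a compliant SPF patient falls below 100% concordance while an uninterrupted PBF patient does not

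*Protocol article*

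**What the plan says.** All statements are in the protocol article.

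- **Run-in (2.7.5.1 Exposure metrics).** "All participants receive a short-peptide formula from enrollment through study Day 3", and "this run-in period is not included in exposure analyses". The exclusion is tied to the end of Day 3, not to the moment of the switch.
- **Window (2.7.5.1).** Its length is "elapsed time from randomization (D4) to 23:59 on D7 or to ICU transfer/discharge or death, whichever occurs first".
- **Adherence (2.7.5.1).** Hours during which the randomized formula was actually given, divided by window hours, times 100. Interruptions are time-stamped, and the calculation is said to rest on hours actually accrued in the window.
- **Arms (2.6.1 and 2.6.2).** The PBF arm carries on with the run-in formula. For the SPF arm the instruction is "Transition from a PBF to an SPF after randomization". Both are fed by continuous pump. No deadline or allowance for the change is given.
- **Contamination (2.7.5.2).** "any administration (any dose, any single occasion) of a formulation not matching the randomized assignment is classified as contamination"; it is a yes/no variable per patient, with event counts also recorded.
- **Fidelity (2.7.5.3).** "Primary adherence is reported as the proportion of participants with 100% concordance", with the continuous adherence percentage as a secondary measure.
- **Use (2.7.5.4 and 2.8.2).** Contamination rate, fidelity and window length are promised for CONSORT reporting. Section 2.8.2 makes them exploratory and descriptive, with 95% confidence intervals and no testing.

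**The concern.** The two arms do not start the window in the same state. A PBF patient can be concordant from the first minute. An SPF patient cannot be until the new formula is running, and that step comes after the clock has started. A rule that tolerates no gap at all therefore falls on one arm for a reason unrelated to how well the trial was run.

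A second problem affects both arms. If the denominator is elapsed time, a feed stopped for a procedure or for intolerance lowers adherence even when no other formula was given. Cessation of enteral feeding is also a component of the feeding-intolerance outcome in 2.7.2. The adherence figure would then partly measure tolerance and not use of the assigned formula.

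At stake is how readers judge treatment separation. In an open-label comparison of two formulas, fidelity and contamination show whether the arms received different treatments. Figures that differ by arm because of a definition would mislead on that point.

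**Working it through.** The plan gives no expected value for these metrics, so there is no figure to reproduce. The check applies the plan's own definitions to a patient who does everything asked.

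**Inputs from the article.** The window W runs from randomization on Day 4 to 23:59 on Day 7. If the patient stays in the ICU, W = (24 − clock hour of randomization) + 72 h, which lies between 72 and 96 h. Randomization at 12:00 gives 12 + 72 = 84 h.

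**Assumptions (not in the article).** L is the delay from randomization to the first SPF feed, f is the share of SPF patients with PBF still running after randomization, and b is the true crossover rate.

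**Step 1, concordance.** Before the first SPF feed, concordant hours are zero whether PBF is running or the pump is off. For an SPF patient with no other interruption:

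adherence = (W − L) / W × 100

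| L | W = 72 h | W = 96 h |
|---|---|---|
| 0.5 h | 99.3% | 99.5% |
| 1 h | 98.6% | 99.0% |
| 2 h | 97.2% | 97.9% |
| 4 h | 94.4% | 95.8% |
| 12 h | 83.3% | 87.5% |

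For example, (72 − 2)/72 = 97.2% and (96 − 2)/96 = 97.9%. The equivalent PBF patient has L = 0 and scores 100%. The continuous measure loses little for a short delay, but the 100% criterion fails for every L above zero.

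**Step 2, contamination.** The rule needs a non-matching formula to be given, so it depends on f:

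SPF contamination rate = 1 − (1 − b)(1 − f)

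With b = 5%:

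| f | SPF arm | PBF arm |
|---|---|---|
| 0 | 5% | 5% |
| 0.5 | 52.5% | 5% |
| 0.9 | 90.5% | 5% |
| 1 | 100% | 5% |

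The article does not give f. If the pump is stopped before randomization and restarted with SPF, f = 0 and no excess arises. Only the SPF arm can be flagged by this route.

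**Step 3, interruptions.** With W = 84 h and one assumed 4 h stop, a patient in either arm who never receives the other formula scores (84 − 4)/84 = 95.2% and fails the 100% criterion. The sentence about accrued hours does not say whether the 4 h leave the denominator. If they do, the score is 80/80 = 100%.

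**Step 4, after the repair.** Suppose both windows open after a common allowance A and the denominator is hours on any enteral formula. An SPF patient who has changed over by A then scores 100% and is not contaminated, like the PBF patient. The contamination rate from this source returns to b in both arms.

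**The case against.** The case on the other side has five parts.

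**PBF at randomization is inferred.** A reader might conclude that every SPF patient is still receiving PBF when the window opens, so that the whole arm is contaminated by construction. The article does not say so. It describes PBF as the formula of study days 1–3, and a paused pump triggers no contamination. This objection stands: the contamination half is conditional. It remains likely, because the feed is a continuous infusion, the change is placed after randomization, and nothing calls for stopping PBF beforehand.

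**The 100% rule has another reading.** Fidelity is defined as full execution of the feeding plan, and for the SPF arm that plan includes the change. The text also does not expressly equate 100% concordance with an adherence percentage of 100. This is fair, but the same definition requires the randomized formula for the whole window, and the only formula for concordance is the hours ratio. An analyst following the text would fail the compliant SPF patient.

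**Interruptions may already be handled.** The accrued-hours sentence could mean that stops are removed. It is unclear either way, and the point applies to both arms, so it does not add to the asymmetry.

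**The consequences are small.** The measures are exploratory and untested, event counts accompany the yes/no flag, and the primary analysis uses none of them. This stands and limits the weight of the point.

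**Clock conventions can be left to a fuller document.** That would answer a mere omission. Here the article itself fixes the start of the window, the any-dose rule and the 100% criterion, and together they give different scores to equally compliant patients.

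**Conclusion.** The concern holds in a limited form. For 100% concordance the asymmetry follows from the definitions as written: any positive changeover delay fails a compliant SPF patient, while an uninterrupted PBF patient passes. The delay lengths are assumptions, but the classification does not depend on them. For contamination the effect ranges from none to the entire SPF arm, depending on whether PBF is still running after randomization. The handling of interruptions is unclear in both arms.

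A reader might also infer that the Per Protocol Set would lose SPF patients selectively. The text does not support that. Section 2.8.2 asks for at least 72 h of the allocated intervention and no major deviations, and does not name contamination as one. The risk arises only if it were later treated as one.

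The intention-to-treat primary analysis is unaffected. This should be corrected because the figures are promised for CONSORT reporting, but it does not threaten the main result.

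**What to change.** 1. In 2.7.5.1 to 2.7.5.3, open the contamination and fidelity window in both arms at randomization plus one common, prespecified changeover allowance. This is a counting convention only. Its length is for the trial team to set, and it need not alter how or when feeding is changed.
2. Define adherence as hours on the assigned formula divided by hours on any enteral formula within that window. State how patients with no enteral hours in the window are shown, since the ratio is then undefined.
3. Report interruption hours with reasons, and changeover time, as separate descriptive items by arm.
4. State that the protocol-directed changeover is neither contamination nor a deviation for the Per Protocol Set.

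The cost is wording. Time-stamps for interruptions and for non-assigned formula are already planned, and the start of SPF is needed anyway to count concordant hours. The downside is that a slow changeover inside the allowance no longer counts as contamination, which is why changeover time must be reported.

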##### Intervention fidelity (adherence)

2.7.5.3

Fidelity is defined as complete execution of the feeding plan with the randomized formulation throughout the exposure window. Primary adherence is reported as the proportion of participants with 100% concordance; a secondary, continuous measure uses the adherence % defined above. If the attending physician changes the formulation for clinical reasons (e.g., fluid restriction, significant feeding intolerance), the reason must be documented, along with: start/stop timestamps of non-assigned formula, total time on non-assigned formula, and total exposure-window hours. Data sources: electronic medical records and clinical study report forms.

##### CONSORT reporting

2.7.5.4

We will report (i) contamination rate, (ii) intervention fidelity, and (iii) duration of the exposure window (hours).

### Data collection and analysis

2.8

#### Data collection

2.8.1

We will use electronic forms to collect relevant clinical information of enrolled patients. Once the data is entered, it cannot be modified. The data entry will be completed by full-time scientific research team members of the Department of Critical Care Medicine of the First Hospital of Jilin University. They will not participate in the clinical treatment of patients and the analysis of the final data.

#### Data analysis

2.8.2

All statistical analyses will be conducted in accordance with a pre-specified statistical analysis plan. The primary analysis will follow the intention-to-treat (ITT) principle The Full Analysis Set (FAS) will include all participants who were successfully randomized and entered the intervention period, provided that they have a valid assessment of the primary outcome (caloric intake on day 7) or sufficient information to derive this value. The Per Protocol Set (PPS) will be a subset of the FAS, including participants who received the allocated intervention for at least 72 h and had no major protocol deviations. The PPS will be used for sensitivity analyses to assess the robustness of the primary findings. The SS will include all participants who received at least one dose of the study intervention and will be used for safety analyses.

The primary outcome, caloric intake on day 7 (continuous variable), will be analyzed using a linear regression model. The model will include the intervention group and the predefined covariates (APACHE II score, BMI, AGI grade, and primary diagnosis) as fixed effects. As this is a single-center randomized controlled trial, no random effects will be specified. To account for potential model misspecification and heteroscedasticity, heteroskedasticity-robust (sandwich) standard errors will be used for statistical inference. If the model residuals show substantial deviation from normality or are influenced by outliers, data transformation (for example, logarithmic transformation) or a nonparametric bootstrap method will be applied in sensitivity analyses to assess the robustness of the results.

Continuous secondary outcomes (e.g., the number of days without a ventilator in the ICU) will be analyzed analogously using linear regression models; secondary binary outcomes (e.g., FI) will be analyzed using a generalized linear model (GLM) with a logit link function. The model will include the intervention group and the pre-specified covariates as fixed effects. As this is a single-center study without inter-center or clustering structures, no random effects will be specified. In addition, because FI is a composite secondary endpoint, each FI component will be reported and analyzed separately alongside the composite FI outcome.

Continuous variables will be summarized as mean ± SD if normally distributed, or as median and interquartile range (IQR, P25–P75) if not normally distributed. Between-group differences in continuous variables will be tested using the independent samples t-test for normally distributed data or the Mann–Whitney U test for non-normally distributed data. Categorical variables will be compared using the Chi-square test.

To assess whether between-group differences in caloric adequacy and tolerance reflect intrinsic physiological effects of the enteral formulas or are confounded by differences in feeding tolerance management, we will compare key nutrition-support process indicators (time to EN initiation; FIS-guided feeding-rate adjustments every 4–6 h; use of prokinetic and/or anti-diarrheal agents; post-pyloric feeding) between groups during the intervention period and will add these as covariates for adjusting confounding factors. At the same time, we will conduct sensitivity analyses to test the robustness of the results.

Sensitivity analyses will include: (I) an unadjusted GLM including only the treatment factor; (II) a covariate-augmented GLM including the prespecified covariates APACHE II score, AGI grade, BMI, primary diagnosis as well as baseline mechanical ventilation. (III) Key treatment indicators include time to initiation of enteral nutrition, feeding-rate adjustments at 4–6-h intervals based on the FIS score, use of prokinetics or antidiarrheals, and use of post-pyloric feeding. All covariates are prespecified and will be retained in the models regardless of statistical significance.

Adjusted odds ratios (ORs) with 95% confidence intervals (CIs) will be reported for binary outcomes, with standardized marginal risk differences provided as supplementary estimates. The primary endpoint will be tested at a two-sided *α* = 0.05 level without multiplicity adjustment. For prespecified secondary clinical endpoints, the false discovery rate (FDR) will be controlled at q = 0.05 using the Benjamini–Hochberg procedure based on two-sided *p* values from the specified models.

Process outcomes (such as fidelity, exposure, and contamination) will be treated as exploratory outcomes and summarized descriptively with 95% CIs; no hypothesis testing or multiplicity correction will be applied to these exploratory analyses.

All analyses were performed using R software (version 4.4.2; R Foundation for Statistical Computing, Vienna, Austria) within RStudio (version 2024.12.1+563; Posit Software, Boston, MA, USA). Two-sided *p* values <0.05 were considered statistically significant.

Given the potential for confounding and co-interventions inherent in nutritional interventions, strong causal inferences will not be made. Primary and secondary analyses are prespecified to be interpreted as estimates of association following adjustment for predefined covariates and sensitivity analyses. Any residual between-group differences will be reported cautiously.

The robustness of between-group differences will be evaluated after adjustment for prespecified clinical covariates and key management-related variables (e.g., tolerance management and feeding strategies). Attenuation of associations after adjustment may suggest partial explanation by management factors, whereas consistency of findings across sensitivity analyses may be considered compatible with potential formula-related differences; however, all conclusions will remain cautious.

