#### Missing data and interpolation strategies

2.8.3

The proportion of missing data for the primary outcome (caloric intake on day 7) is expected to be approximately 15%, mainly due to discharge, transfer, or incomplete records. The primary analysis will be conducted in the FAS using multiple imputation (MI) under the missing-at-random (MAR) assumption. The imputation model will include treatment group, APACHE II score, BMI, AGI grade, primary diagnosis, and other variables related to missingness or the outcome.

As sensitivity analyses, a complete-case analysis (including only participants with observed day-7 outcomes) will be performed. In addition, PPS analysis and delta-adjusted MI analyses will be conducted to assess the robustness of the results under alternative missing data assumptions.

If the results are consistent across analyses, the study findings will be considered robust.

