This study has several notable strengths. 1. To our knowledge, this is the first large randomized controlled trial to address whether, in critically ill patients with AGI whose intestinal function has recovered or at least not worsened, a transition from a PBF to an SPF is necessary. 2. We selected actual caloric intake as the primary endpoint to directly capture the impact of formula type on achieved nutrition, and we complemented this with a broad set of secondary outcomes—including actual protein intake, feeding tolerance, nutritional serum biomarkers, intestinal injury markers, trajectories of muscle mass, and key clinical endpoints—to provide a comprehensive and systematic evaluation. 3. Conducting the trial at a single center is expected to enhance consistency in the feeding protocol and ultrasound measurements. 4. To reduce heterogeneity and confounding, we excluded patients with hepatic or renal disease and those receiving extracorporeal therapies, conditions known to influence metabolism and nutritional requirements (23). 5. Moreover, clinical data are collected by an independent research team that is not involved in patient care, randomization, or data analysis, thereby minimizing subjective bias.

This study also has important limitations. 1. The single-center design may limit external validity and generalizability. 2. Our primary endpoint—caloric intake on ICU Day 7—introduces a risk of missing data among patients who are discharged or die before Day 7; these cases require imputation, which may deviate from true values. 3. Despite standardized training based on the guideline, some team-level subjectivity in implementation is unavoidable and could affect delivered feeding volumes or tolerance management. Although we will adjust for prespecified covariates, co-interventions and variability in feeding strategies may still influence the results, and residual confounding cannot be excluded. Our findings will be interpreted cautiously. 4. Finally, due to resource constraints, indirect calorimetry was not used to set energy targets, which may reduce the precision of prescribed goals.

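### The Full Analysis Set is conditioned on a Day-7 caloric value being assessed or derivable, which contradicts the intention-to-treat principle and the primary multiple imputation planned in that same set

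*Protocol article*

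**What the plan says.** Section 2.8.2 (Data analysis) of the protocol article states: "The primary analysis will follow the intention-to-treat (ITT) principle". It then defines the FAS by two conditions beyond randomisation. The set holds "all participants who were successfully randomized and entered the intervention period", and these patients qualify only "provided that they have a valid assessment of the primary outcome (caloric intake on day 7) or sufficient information to derive this value". The section does not say what information is sufficient, or how a derived value differs from an imputed one.

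Section 2.8.3 (Missing data and interpolation strategies) gives the expected loss: "The proportion of missing data for the primary outcome (caloric intake on day 7) is expected to be approximately 15" per cent, "mainly due to discharge, transfer, or incomplete records". On the primary method it says: "The primary analysis will be conducted in the FAS using multiple imputation (MI) under the missing-at-random (MAR) assumption". As a sensitivity analysis, "a complete-case analysis (including only participants with observed day-7 outcomes) will be performed". The per-protocol and delta-adjusted imputation analyses are further checks, and consistent results across them will be read as robustness.

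The Discussion (section 3), in its list of limitations, names patients who leave or die before Day 7 and says "these cases require imputation, which may deviate from true values".

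**The concern.** Sections 2.8.2 and 2.8.3 use one analysis set for two incompatible purposes. Section 2.8.2 lets a patient in because the Day-7 value exists or can be derived. Section 2.8.3 needs patients in the set whose Day-7 value is missing.

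Two things are at stake. First, randomisation takes place on study Day 4, so having a Day-7 record in the ICU is a post-randomisation event. It is tied to recovery, transfer and death, which the allocated formula might influence, and the treatment is open-label. Selecting on that event gives up the protection of randomisation. The condition on entering the intervention period is also applied after randomisation. Second, the sensitivity analyses are meant to test the missing-data assumption. If the patients with missing outcomes are removed beforehand, those analyses have little left to test, yet their agreement would be reported as robustness.

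**Working it through.** **1. The statements side by side.**

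| Place | What it requires |
|---|---|
| 2.8.2, principle | Patients analysed as randomised |
| 2.8.2, FAS | Intervention period entered, and Day-7 value assessed or derivable |
| 2.8.3, primary analysis | About 15% of Day-7 values missing, imputed within the FAS |
| 2.8.3, sensitivity | Complete-case analysis, distinct from the primary |
| Discussion, limitations | Early discharges and deaths are imputed |
| Abstract, Participants | 496 patients in the final analysis |

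Only the FAS row points towards excluding patients without a Day-7 value. Section 2.7.5.1 (Exposure metrics) confirms that the plan foresees ICU transfer, discharge or death within Days 4 to 7.

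**2. Two readings of the derivation clause.**

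- *Derivation means calculation from partial Day-7 records.* A derived value is no longer missing, and patients gone before Day 7 stay outside the FAS. Few or no outcomes remain to be imputed.
- *Derivation includes imputation.* The condition then excludes almost nobody and does no work.

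Two analysts could defend different primary populations from the same sentence.

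**3. How many patients.** Inputs: planned N = 496 (section 2.5) and 15% missing (section 2.8.3).

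- Missing: 496 × 0.15 = 74.4, about 74.
- Remaining: 496 − 74 = 422.

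This is the upper end. It applies the 15% to all 496 and takes no missing value as derivable. The document gives no number for patients who might fail to enter the intervention period.

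**4. Power at the two set sizes.** Inputs from section 2.5: difference 24.9 − 22.4 = 2.5 kcal/kg/day; SDs 9.825 and 9.1; two-sided α = 0.05.

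- Common SD = √[(9.825² + 9.1²)/2] = 9.469.
- Power ≈ Φ[2.5 / (9.469 × √(2/n)) − 1.96], with n per group.
- The plan's own n = 225: power 0.80, not the stated 0.90. That is a separate matter, and this point does not rest on it.
- n = 211 (422 in total): power 0.77.
- n = 248 (496 in total, all fully informative): power 0.84.

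With about 74 values imputed, power lies between 0.77 and 0.84, depending on how well the imputation model predicts intake.

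**5. Bias, as illustration only.** If missing and observed patients differ in mean intake by D in both arms, and the missing share differs between arms by p, dropping the missing shifts the unadjusted contrast by p × D. The document gives neither quantity. Assuming D = 5 kcal/kg/day and p = 0.05 to 0.10:

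- 0.05 × 5 = 0.25 and 0.10 × 5 = 0.50 kcal/kg/day.
- 0.25/2.5 = 10% and 0.50/2.5 = 20% of the planned difference.

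**6. Effect on the sensitivity analyses.** In the literal FAS, the complete-case analysis differs from the primary only by the derived values. Delta-adjusted imputation has few or no missing outcomes to shift. The per-protocol set is a subset of the FAS (section 2.8.2) and inherits the same selection.

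**The case against.** The strongest reply is that the intent to impute is plain. Section 2.8.3 names imputation as primary and complete-case as sensitivity, and the Discussion says that early departures will be imputed. A single clause in section 2.8.2 stands against this. That clause also admits patients whose value can be derived, which could cover incomplete records, one of the three listed causes of missingness. If derivation were read to include imputation, the conflict would disappear. This is generous but not excluded. It does not save the wording, because the clause would then have no function.

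A reader might infer that the primary analysis *is* complete-case and that imputation has nothing to act on. The document does not support that. It leaves the contradiction open, and the collapse follows only if section 2.8.2 is applied literally. Even then it is approximate: patients with derived but unobserved values sit in the FAS and outside the complete-case set, and any missing covariates could still be imputed. For the same reason, agreement between the two analyses would be largely built in, but not automatic.

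A reader might also take the 0.25 to 0.50 kcal/kg/day as the cost of the defect. It is not. Both inputs are assumed, and correcting the FAS alone would not recover that amount. The four covariates named for the imputation model (APACHE II, BMI, AGI grade, primary diagnosis) are the same four in the primary regression. When only the outcome is missing, imputing from those covariates gives essentially the complete-case estimate. Any gain must come from the further variables that section 2.8.3 allows but does not name.

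Finally, whether a death before Day 7 should be treated as missing at random is a question about the estimand. It is separate from this contradiction.

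**Conclusion.** The contradiction stands. The FAS definition conflicts with the intention-to-treat principle in the same section, with the primary imputation in section 2.8.3, and with the intent stated in the Discussion. It is not a detail left to an analysis plan: the article itself prints the conflicting statements, and a plan that follows one must depart from another.

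The consequence is conditional. If section 2.8.2 is applied as written, up to about 74 of 496 randomised patients are left out on a post-randomisation event, assuming that 15% of all 496 lack a Day-7 value and none is derivable. The primary analysis then becomes roughly complete-case, and its complete-case and delta-adjusted checks lose most of their value. No bias can be quantified from the document; the figures in the working are illustrative. Confidence is high in the contradiction, and lower in which reading the investigators would follow.

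**What to change.** - Define the FAS as all randomised patients, analysed in their allocated arm. Delete the conditions on Day-7 availability and on entering the intervention period.
- State that deriving a Day-7 value means calculating it from partial Day-7 records, as distinct from imputation.
- Run the primary multiple imputation in that set. Include post-randomisation intake before Day 7 as auxiliary variables where it is recorded; section 2.8.3 already allows variables related to the outcome. Without such variables, imputation will add little to the complete-case estimate.
- Keep complete-case as the sensitivity analysis.

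The redefinition costs a wording change in the protocol and analysis plan and needs no new data. The auxiliary variables depend on whether intake on Days 4 to 6 is captured. The visible text does not list it, and the schedule table is not shown, so this needs checking. The change does not bring power to 0.90. It should be settled before outcome data are examined, because it decides who enters the primary analysis.
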